### Statistical methods

#### Analysis strategy

The analysis of clinical efficacy will make use of intention-to-treat analysis. The Last-Observation-Carried-Forward (LOCF) method will be used for handling missing data. An initial comparison will be made between both groups, examining key variables to establish the groups’ baseline comparability after randomization. To describe the quantitative variables, means and standard deviations will be calculated when they fulfil normality criteria. The Chi-squared test will be used for qualitative variables such as a number of socio-demographic ones. The differences between clinical variables at baseline, one month, three months and six months will be calculated using analysis of covariance (ANCOVA) adjusted by baseline.

To study the main variable, analysis of variance will be performed on repeated measurements, including all the evaluations over time. The main variable (pain perception) will be taken to be a continuous variable for this purpose. The models will include adjustments for the baseline pain value and for any other variable that may have shown differences in the baseline measurement. Possible group × time interactions will be studied by means of Mixed Factor ANOVA. Additionally, linear regression models will be used to compare the differences between the two groups for each of the evaluations over time as compared to baseline. Similar analyses will be performed on the other secondary clinical variables.

To analyze the differences found by the neuroimaging test (spectrometry) taken at baseline and at six months follow-up, Student’s *t*-test for paired measurements will be calculated. The relation between neuroimaging variables and clinical variables will be assessed by means of Spearman’s Rho non-parametric test.

In case of lost values, a sensitivity analysis will be made to estimate the effect of the lost values on the results. These values will also be replaced using several approaches, such as last recorded values and imputations. Statistical analyses will be performed with the Statistical Package for the Social Sciences (SPSS) 19.0 statistical software package (SPSS Inc., [name]), with *P-*values below 0.05 considered significant.

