**Recruitment & Clinical assessment**				
Signing of informed consent	X			
Diagnosis	X			
Inclusion/exclusion criteria	X			
Sociodemographic variables	X			
Pain assessed with sphygmomanometer	X	X	X	X
Pain assessed with Analogue Visual Scale	X	X	X	X
Cognitive function (assessed with MEC)	X	X	X	X
Global function (evaluated by FIQ)	X	X	X	X
Anxiety and depression (assessed with HADS)	X	X	X	X
Quality of life (assessed by EuroQol 5D)	X	X	X	X
Clinical Global Impression (CGI)	X	X	X	X

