### Sample size

The choice was made to have a sample comprising 70 subjects (n = 35 subjects in each of the two treatment groups) because this sample size will enable us to obtain reliable results and to ensure that both treatment groups are of equal sizes at the start of the study. Smaller sample sizes have been used in the identification of significant differences in glutamate levels in different brain regions between FM patients and controls.

Using the results of the pilot study and taking reduction of pain (as determined using the Pain Visual Analogue Scale and sphygmomanometry) as the primary variables, a pre-intervention mean score of 56 (SD 14.9) was obtained with the VAS, and 104 (SD 30.8) with sphygmomanometry. After treatment, the means decreased to 44 (SD 16.9) and 85 (SD 20.6), respectively. Therefore, assuming a 95% confidence interval and a power of 80%, we find that we require a sample size of 28 individuals in each group for the VAS finding and of 30 individuals in each group for the reduction measured by sphygmomanometry. The resulting sample size that will enable us to analyse the final variable will be 60 individuals, with 30 being assigned to each of the two groups. Based on previous studies (personal communication), an attrition rate of 10% can be expected. Therefore, the final number of recruited patients will be 35 patients for each arm.

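### No visit or contrast is named to decide the VAS pain result, so several tests at 0.05 lift the false-positive rate above 5%; read literally, baseline is also an outcome, which shrinks the estimate by a quarter

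*Protocol article*

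**What the plan says.** The Main outcome variables section names perceived pain on a 0 to 100 VAS as the main efficacy variable and gives no time point. Table 1 has the row "Pain assessed with Analogue Visual Scale" marked at baseline and at 1, 3 and 6 months.

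The Analysis strategy section then sets out these analyses:

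- ANCOVA of the clinical variables, adjusted by baseline. The time points listed are baseline, 1, 3 and 6 months.
- For the main variable: "analysis of variance will be performed on repeated measurements, including all the evaluations over time".
- On covariates: "The models will include adjustments for the baseline pain value".
- A group-by-time interaction by mixed-factor ANOVA.
- In addition: "linear regression models will be used to compare the differences between the two groups for each of the evaluations over time", as compared with baseline.

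The only decision rule is that P-values below 0.05 count as significant. The section gives no order among these analyses beyond introducing the repeated-measures ANOVA as the way to study the main variable, and it gives no multiplicity rule.

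**The concern.** A trial planned around one primary comparison at 5% should say which comparison that is. Here a significant group effect, a significant interaction, or a significant difference at month 1, 3 or 6 could each be reported as a positive result on the main variable, and the text would not rule any of them out. The chance that at least one is significant when memantine does nothing is then above 5%.

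There is a second, separate question about the estimate. If all evaluations really means all four VAS rows of Table 1, the outcome includes baseline, where randomization makes the expected difference zero. A group effect averaged over those four values understates the effect on treatment.

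**Working it through.** **1. The plan's own figure.** The Sample size section reports that "a pre-intervention mean score of 56 (SD 14.9) was obtained with the VAS, and 104 (SD 30.8) with sphygmomanometry", and then: "After treatment, the means decreased to 44 (SD 16.9) and 85 (SD 20.6), respectively". For VAS:

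- Difference: 56 − 44 = 12.
- SD: √((14.9² + 16.9²)/2) = √253.81 = 15.93.
- n per group = 2 × (1.960 + 0.842)² × 253.81 / 12² = 27.7, so 28.

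For sphygmomanometry the difference is 19 and the SD is 26.20, which gives 30. Both match the stated result: "we require a sample size of 28 individuals in each group for the VAS finding and of 30 individuals in each group". The calculation is therefore for one comparison of two means at 80% power. Two-sided 0.05 is inferred, because one-sided testing would give 22 and 24.

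**2. Counting the tests of VAS pain.**

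- Three post-baseline ANCOVAs.
- One repeated-measures group effect.
- One group-by-time interaction.
- Three per-visit regressions.

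Whether the regressions are extra tests depends on their covariates. If change from baseline is regressed on group and baseline, the group coefficient and P-value are identical to those of the ANCOVA at that visit; only the baseline slope moves, by −1. There are then five distinct tests. If the regressions omit baseline, there are eight.

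**3. False-positive rate with no treatment effect.** Inputs: 35 per arm (Sample size section), four visits (Table 1) and SD 15.9 (step 1). The within-patient correlation is assumed, because the article gives none. There were 8,000 simulated trials per row. The interaction is from the four-visit mixed ANOVA with Greenhouse-Geisser correction. Each entry is the chance of at least one P below 0.05.

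| Correlation | 3 ANCOVAs | Group effect or interaction | ANCOVAs + both | + regressions without baseline |
|---|---|---|---|---|
| 0.3 | 0.142 | 0.091 | 0.166 | 0.214 |
| 0.5 | 0.140 | 0.091 | 0.159 | 0.202 |
| 0.7 | 0.132 | 0.082 | 0.148 | 0.179 |
| 0.7, autoregressive | 0.122 | 0.082 | 0.144 | 0.172 |

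Reference values for independent tests are 1 − 0.95² = 0.0975 for two and 1 − 0.95³ = 0.143 for three. Any single baseline-adjusted visit test ran at 0.046 to 0.054. The simulation error on 0.214 is √(0.214 × 0.786/8000) = 0.0046, so the top of the last column is about 0.22. A second simulation with 31 per arm gave 0.124 to 0.139 for the ANCOVAs, 0.156 to 0.162 with both repeated-measures tests, and 0.189 to 0.204 with the unadjusted regressions.

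**4. Baseline as outcome and covariate.** Let Y0 be baseline and M the mean of the three post-baseline values. The four-visit mean is (Y0 + 3M)/4. Regress it on group and Y0. The Y0 part is fitted exactly by the covariate and contributes nothing to the group coefficient. That coefficient is therefore ¾ of the coefficient for M, and its standard error is also ¾. The ratio, and so the P-value, is the same.

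Simulation at correlation 0.5 with a constant 12-point benefit confirms this:

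- Estimates: 9.0 with four visits against 12.0 with three.
- Standard errors: 1.839 against 2.453, a ratio of 0.75.
- Power: 0.997 for both.

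With no effect, the four-visit adjusted test kept its level (0.049 to 0.052).

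**The case against.** **The plan does imply a priority.** The repeated-measures ANOVA is introduced as the analysis of the main variable, the interaction as a possibility and the regressions as an addition. The ANCOVA sentence concerns clinical variables in general. This stands as far as it goes, and it is why the narrowest figure is 8 to 9%. It does not settle the matter. A repeated-measures ANOVA yields both a group effect and an interaction, the text does not say which one decides, and neither is an effect at a named visit.

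**The article condenses a fuller document.** Covariance structure and similar detail can be left out. The deciding visit and contrast define the question, and here the article describes several routes to an answer on the main variable under a single significance rule.

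**Stronger readings that the article does not support:**

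- *That one in five null trials would give a positive pain result.* This needs regressions without baseline. The sentence on baseline adjustment comes just before the regressions and may cover them. If so, they add nothing.
- *That using baseline twice inflates false positives.* Step 4 shows that it does not. The inflation comes from the number of tests and the open choice among them.
- *That the plan certainly puts baseline in the outcome.* This is the literal reading with Table 1, and the ANCOVA sentence points the same way. But the regression sentence speaks of evaluations compared with baseline, which fits post-baseline visits only.
- *That power is lost.* Power falls only for a four-visit group effect without the covariate (0.93, 0.85 and 0.76 at correlations 0.3, 0.5 and 0.7 with a constant 12-point effect). The plan states adjustment and does not state that test.
- *That the estimate is half the month-6 effect.* That needs an assumed build-up of 4, 8 and 12 points, which no figure in the article supports. Part of the fall (12 to 8) is ordinary averaging over treatment visits, which is a legitimate target if chosen in advance.

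**Conclusion.** The point holds in two separate parts.

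**Multiplicity.** No visit or contrast is named as decisive for the main variable, and every test is judged at 0.05. The false-positive rate is about 8 to 9% if either repeated-measures result is accepted, and about 14 to 17% if the three visit ANCOVAs also count. It is about 17 to 22% only if the regressions are not adjusted for baseline. These figures rest on assumed within-patient correlations of 0.3 to 0.7 and on no missing data. They do not depend on the baseline question.

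**Estimate.** On the literal but not the only reading of the repeated-measures sentence, the group main effect and its confidence interval shrink by exactly one quarter. Test level, P-value and power are untouched. The group-by-time contrast is not averaged in this way and is not diluted.

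The first part should be settled before unblinding, because it decides what may be claimed. The second needs a clarifying phrase.

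**What to change.** Name one primary contrast at one visit. One suitable choice is the memantine-placebo difference in VAS pain at month 6, adjusted for baseline VAS. It matches the six-month follow-up and the second spectroscopy assessment.

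- State that the outcomes are the values at months 1, 3 and 6 only, with baseline VAS as a covariate, and remove baseline from the time points listed in the ANCOVA sentence.
- Label months 1 and 3, the group-by-time test, any effect averaged over visits and the per-visit regressions as supportive.
- Say whether the regressions adjust for baseline. If they do, note that they repeat the ANCOVA.

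The cost is wording; no new data are needed. The downside is small: an early-visit or averaged result can no longer be claimed as primary. If the contrast is taken from a mixed model for repeated measures, that model handles missing visits in its own way, and the text must reconcile this with the stated LOCF rule. A baseline-adjusted ANCOVA at month 6 would target the same contrast without changing the model family already named.

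### Apart from baseline pain, covariates for the main-variable models are chosen because the arms happen to differ at baseline, not because they are expected to predict pain

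*Protocol article*

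**What the plan says.** All the relevant text is in the protocol article, Statistical methods, Analysis strategy.

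- A comparison of the arms comes first: "An initial comparison will be made between both groups, examining key variables to establish the groups’ baseline comparability after randomization". The key variables are not listed.
- The main analysis is then described: "To study the main variable, analysis of variance will be performed on repeated measurements, including all the evaluations over time".
- The covariate rule follows. The models adjust for baseline pain and also "for any other variable that may have shown differences in the baseline measurement".
- The approach carries over to other outcomes: "Similar analyses will be performed on the other secondary clinical variables".
- The only significance level in the section is the general one, P-"values below 0.05 considered significant". It is not tied to the covariate rule.

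The section on randomisation, allocation and masking describes a concealed computer-generated sequence and names no stratification factor that would supply further covariates. I found nothing elsewhere in the article that overrides the rule.

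**The concern.** Under concealed randomisation, baseline differences between the arms are chance. Comparing the arms cannot establish comparability in any useful sense. The size of a difference also says nothing about whether the variable predicts later pain, which is what makes a covariate worth having. The rule can therefore err both ways: it can admit a variable unrelated to pain because the arms drifted apart on it, and it can leave out a strong predictor because the arms happen to match.

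Two things are at stake. First, apart from baseline pain, the content of the primary model is not settled until baseline data have been split by arm. Second, with about 60 analysable patients, the trial gives up precision that covariates chosen in advance could provide.

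**Working it through.** **1. The plan's own figures.** The only design calculation is in the Sample size section; it uses 80% power and a 95% confidence level. I take n per group = 2 × (1.960 + 0.842)² × SD² / difference², with SD² the mean of the two pilot variances.

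- VAS: difference 56 − 44 = 12; SD² = (14.9² + 16.9²)/2 = 253.8, so SD = 15.93; n = 2 × 7.85 × 253.8/144 = 27.7, giving 28 as stated.
- Sphygmomanometry: difference 104 − 85 = 19; SD² = (30.8² + 20.6²)/2 = 686.5, so SD = 26.20; n = 2 × 7.85 × 686.5/361 = 29.9, giving 30 as stated.

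These reproduce and do not bear on the covariate rule, to which no figure is attached.

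**2. How many candidates?** The article does not say. With the HADS split into its two subscales, Table 1 names seven scored baseline items besides the VAS: sphygmomanometry, MEC, FIQ, HADS anxiety, HADS depression, EQ5D and CGI. Sociodemographic variables form one row that is not itemised. The key variables could be fewer than seven or more. I assume a range of 5 to 10.

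**3. How often would a covariate enter by chance?** The criterion is not given either; I assume p<0.05. For k independent candidates, the chance that at least one qualifies is 1 − 0.95^k. The last column is a simulation with an assumed pairwise correlation of 0.3.

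| k | Independent | Correlation 0.3 |
|---|---|---|
| 5 | 23% | 21% |
| 7 | 30% | 27% |
| 8 | 34% | 30% |
| 10 | 40% | 35% |

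With five candidates and a correlation of 0.5 the figure is 18%.

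**4. Effect on type I error.** This is an illustrative simulation with assumed inputs: 30 per arm, a single follow-up ANCOVA, baseline pain correlated 0.5 with outcome, and ten independent candidates of which three are prognostic (standardised coefficient 0.35 each). There were 8,000 runs and no treatment effect.

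- Baseline pain only: 5.7% (nominal 5%; the excess is simulation error).
- One fixed p<0.05 imbalance rule: about 4%.
- Smallest p-value from no added covariates or thresholds of 0.05, 0.10 or 0.20: about 7%.

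A repeat with 30,000 runs gave 4.9%, 3.7% and 6.5%, so the pattern is stable.

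**5. Effect on precision.** In the same setting, the SD of the treatment estimate was 0.23 with baseline pain only, 0.22 with the imbalance rule, and 0.16 with the three prognostic covariates fixed in advance. The first and last agree with √(residual variance × 2/30):

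- baseline pain only: residual variance 1 − 0.5² = 0.75, SD 0.224;
- three prognostic covariates: 0.75 − 3 × 0.35² = 0.3825, SD 0.160.

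Three such covariates together explain 37% of the outcome variance, which is generous. With one, the SD is √(0.6275 × 2/30) = 0.205, about 9% lower than with baseline pain only. With two, it is √(0.505 × 2/30) = 0.183, about 18% lower.

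**The case against.** The strongest reply is that this is an article. A list of candidates and a threshold are details that a full protocol or SAP would normally hold, and baseline pain, an obvious covariate, is already fixed. Both points stand as far as they go. The missing list and threshold are not the finding, and the primary model is not wholly open. But the article does state the principle of selection. A SAP that supplied a threshold would still be selecting on chance imbalance.

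Some stronger readings are tempting and are not supported:

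- *That the model is chosen from unblinded data.* The comparison needs data split by arm, which coded labels can provide. No section says that the analyst is unmasked.
- *That the rule inflates the false-positive rate.* Applied rigidly at p<0.05 it did not. Inflation appeared only when the best of several criteria was taken, which the wording permits but does not prescribe.
- *That needless covariates cost appreciable precision.* At 5% each, ten candidates add 0.5 covariates on average. In a separate simulation with all ten irrelevant, the SD of the treatment estimate rose from 0.224 to 0.230, about 3%. The real loss is the precision forgone.
- *That the model would change by chance in more than one trial in three.* That needs eight or more independent candidates, or about ten at a correlation of 0.3. Table 1 names seven scored items, which give 30%.
- *That baseline HADS depression is an established prognostic covariate.* The Discussion reports that glutamate correlates with depression and with pain. It does not say that baseline depression predicts later VAS.

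**Conclusion.** The point holds for the additional covariates only. The stated rule selects them on chance differences between arms rather than on prognostic value, and the same approach extends to the secondary clinical variables. If a difference means p<0.05, and there are 5 to 10 independent candidates, at least one covariate enters by chance in 23% to 40% of trials (30% for the seven scored items), and in somewhat fewer if the candidates are correlated. Both the criterion and the number of candidates are assumptions.

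The consequence is an avoidable data-dependent primary model and forgone precision. How much precision is forgone depends on how prognostic the available variables are, which the article does not report. This should be changed, but it does not in itself invalidate the primary analysis.

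**What to change.** 1. Delete the clause that adjusts for variables found to differ at baseline.
2. Name the primary covariates in advance: baseline VAS plus, at most, one or two variables already collected, each chosen on prior evidence that it predicts pain, with that evidence cited. If there is none, baseline VAS alone is sufficient.
3. Describe baseline characteristics by arm, and do not use tests to select covariates.
4. Report any model adjusted for observed imbalance as a labelled sensitivity analysis.
5. Apply the same rule to the secondary clinical variables, with each outcome's own baseline value as the fixed covariate.

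The cost is a sentence or two in the Analysis strategy section, settled before baseline data are examined by arm. It needs no new data, visits or patients.

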### Safety and monitoring

Any adverse events and serious adverse events will be recorded and a determination will be made as to whether any medical action required is related with the administered drug. Any adverse event related to the study drug will be recorded and monitored until its resolution or stabilization, and the regulatory notification process will be followed in accordance with the pertinent legislation in force (timeframes, unmasking, and so on). Study participants will be requested to report to the researchers any adverse effect (serious or otherwise) that may arise in the period between visits or any other circumstances that may lead to their withdrawal from the study.

### Ethical aspects

Informed consent will be obtained from the participants before they are aware of which group they are to be included in. Before they give their consent, the patients will be provided with a general overview of the aims and characteristics of the study and the psychological and pharmacological intervention. They will also be informed that they will be participating voluntarily and that they can choose to withdraw at any time with the guarantee that they will continue to receive the treatment considered most appropriate by their doctor.

With regard to the potential risks of the study, data gathering involves no risks to the subjects participating in the study, and the neuroimaging techniques that will be performed are non-invasive techniques that do not place subjects in any danger. With regard to the potential benefits, if the hypothesis of the study, the patients in the treatment group will be able to control their pain during the course of this research. The results will be communicated to the scientific community and to the relevant institutions, which will lead to the expected benefits being obtained for society and for people diagnosed with FM. Nevertheless, there is a possibility that there will be no benefit gained from participating in this study.

The study follows Helsinki Convention norms with posterior modifications, and the Declaration of Madrid of the World Psychiatric Association. The Study Protocol was approved by the Clinical Research Ethics Committee of Aragón (June 2012) and the Medicines and Health Products Agency of Spain (EUDRACT 2011-006244-73).

